## Statistical methods

### Statistical methods for primary and secondary outcomes {20a}

The primary outcome will be analysed between two groups using generalised estimated equations (GEE) using an identity link and binomial family [47], with site as a random effect and sex as a fixed effect. The result will be presented as risk difference with 95% confidence interval. We will state non-inferiority if the lower bound confidence interval does not stretch below −10% risk difference. The first secondary outcome on patients’ perception (ordinal 1–10 scale) will be analysed using a non-parametric Mann Whitney *U* test. The remaining secondary outcomes (all binary) will also be analysed using GEE and reported as a risk difference with 95% confidence interval. Risk differences will be presented in a forest plot. If the telephone interview and the retrospective review report different parameters for the primary outcome (e.g. the patient does not report additional antibiotic prescriptions for UTI, but such prescriptions are identified in the medical chart review), we will always choose the conservative option and consider this a failure.

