**Methods:**

We plan to perform an investigator-initiated non-inferiority trial. Adult hospitalised patients treated with 1–5 days of intravenous antibiotics for acute febrile urinary tract infection caused by extended spectrum beta-lactamase (ESBL) producing Enterobacterales will be randomised 1:1 to either control (7–10 days of either oral ciprofloxacin 500 mg twice daily or oral trimethoprim–sulfamethoxazole 800 mg/160 mg twice daily or intravenous ertapenem 1 g once daily, depending on sex, drug allergy, glomerular filtration rate and susceptibility testing) or intervention (10 days of pivmecillinam 400 mg three times daily and amoxicillin/clavulanic acid 500/125 mg three times daily). The primary outcome will be clinical cure 10 days (+/− 2 days) after antibiotic treatment completion. Clinical cure is defined as being alive with absence of fever and return to non-infected baseline of urinary tract symptoms without additional antibiotic treatment or re-hospitalisation (for urinary tract infection) based on a centralised allocation-blinded structured telephone interview. We plan to recruit 330 patients to achieve 90% power based on a sample size simulation analysis using a two-group comparison, one-sided alpha of 2.5%, an absolute non-inferiority margin of 10% and expecting 93% clinical cure rate and 10% loss to follow-up. The primary endpoint will be analysed using generalised estimated equations and reported as risk difference for both intention-to-treat and per protocol populations. Patients are planned to be recruited from at least 10 centres in Sweden from 2023 to 2026.

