## Methods: participants, interventions and outcomes

### Study setting {9}

We will recruit patients from up to 29 infectious disease (ID) clinics in secondary and tertiary, emergency and teaching hospitals in Sweden. Participant recruitment 2023 in the following five Swedish ID clinics: Helsingborg, Malmö, Lund, Kristianstad and Västerås. A full list of currently recruiting centres will be updated on https://classic.clinicaltrials.gov/ct2/show/NCT05224401 and on the trial homepage: https://pacuti.se/.

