#### Secondary outcomes

Participants’ perception of treatment tolerability on a 1–10 scale.Early study drug discontinuation.Additional antibiotic subscriptions (for UTI) within 28 days from randomisation.Proportion of patients re-admitted to hospital (due to UTI symptoms) within 28 days from randomisation.Drug-related serious adverse events within 28 days from randomisation.All-cause mortality within 28 days from randomisation.Growth of EPE (phenotypically same species) in urine culture (10^3^ CFU/mL) 10 +/− 2 days after antibiotic treatment.Growth of EPE or carbapenemase-producing bacteria in faecal cultures 10 +/− 2 days after antibiotic treatment.

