## Sample size {14}

We expect a clinical cure rate of 93%, based on previous trials on antibiotic efficacy in febrile UTI exploring similar primary outcomes [37, 41]. We have chosen a classic absolute non-inferiority margin of 10% in accordance with the U.S. Food and Drug Administrations (FDAs) recommendation on developing new drugs for complicated UTIs [43]. We consider this to be suitable considering the low severity of all aspects of the composite primary endpoint except for 28-day mortality which we will evaluate specifically as a secondary endpoint and in the interim analysis. When using a one-sided alpha of 2.5% and performing a statistical simulation of 300 enrolled patients in 30 clinics with an intraclass correlation coefficient of 0.1 and generalised estimated equations (GEE) comparison between two groups with a random intercept for site as the primary analysis we reach 90% power. We plan on recruiting 330 patients to allow for 10% loss to follow-up. The study is not powered to infer non-inferiority between the intervention and any single antibiotic in the control group, but only towards the control group as a whole. The secondary objectives should be considered exploratory and are not based on sample size calculations.

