### Interim analyses {21b}

An interim analysis will be performed once half of the patients have been included (*n* = 165). Blinded data will be delivered by an independent statistician to the Data Monitoring Committee (DMC) who will then provide an allocation-blinded recommendation to the trial investigators whether to continue, hold or terminate the trial prematurely. The recommendation is based on safety and futility. Safety is based on three parameters, the number of possibly related serious adverse events, the number of early study drug discontinuations and the number of deaths within 28 days. It is difficult to provide fixed stopping criteria for safety since these events are expected to be very few, and the DMC have to assess frequency, severity and possible relationship to the study drug and give their best advice accordingly. Futility is defined as less than 5% probability of finding non-inferiority in the final analysis based on conditional power simulations as suggested by Bratton et al. [48]. The trial investigators will make the final decision whether to terminate the trial and will have to provide a written account to explain if they do not follow the recommendation from the DMC.

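### 28-day mortality and drug-related SAEs, expected to be very few, are assigned to a GEE risk difference that fails, or can give too low a limit for excess harm, when an arm has no events

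*Protocol article*

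**What the plan says.** The statistical methods section (20a) sets the primary analysis as a GEE with identity link and binomial family, site as a random effect and sex as a fixed effect. It gives tolerability a rank test. For everything else it says: "The remaining secondary outcomes (all binary) will also be analysed using GEE and reported as a risk difference with 95% confidence interval". No exception and no fallback for sparse data is stated.

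The outcomes caught by this rule include "Drug-related serious adverse events within 28 days from randomisation" and "All-cause mortality within 28 days from randomisation" (Secondary outcomes).

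The interim section (21b) bases safety on possibly related SAEs, early drug discontinuations and 28-day deaths, and remarks: "It is difficult to provide fixed stopping criteria for safety since these events are expected to be very few". That sentence is about the interim, but two of its three parameters correspond closely to the two outcomes at issue.

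The sample size section (14) defends the 10% margin by the low severity of the endpoint's components "except for 28-day mortality which we will evaluate specifically as a secondary endpoint and in the interim analysis". It also says: "The secondary objectives should be considered exploratory and are not based on sample size calculations".

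**The concern.** The interval prescribed here takes its variance from the observed events. An arm without events contributes none, so its risk is treated as known to be exactly zero. The protocol therefore fixes a method for two outcomes and elsewhere expects the condition under which that method breaks down.

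At stake is how the final report describes possible harm. The margin rationale sets mortality apart for its own evaluation, and this interval is the final report of that evaluation. If it has no width, cannot be computed or is too short on the harm side, readers learn less about a possible excess of deaths or drug-related SAEs than the data would allow, or see a smaller one.

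**Working it through.** **Inputs.** 330 patients randomised 1:1 gives 165 per arm. The number of sites K is taken from 10 ("Patients are planned to be recruited from at least 10 centres in Sweden from 2023 to 2026") to 29 ("We will recruit patients from up to 29 infectious disease (ID) clinics"). The protocol gives no event risks, so those below are assumptions. It also states no figure for this point that could be reproduced. Differences are the combination (PAC) minus control, in percentage points.

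**Step 1. How often an arm is empty.** P(arm empty) = (1-p)^165, with equal risks in both arms.

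| Risk p | One given arm empty | Both empty | Exactly one empty |
|---|---|---|---|
| 0.5% | 0.437 | 19% | 49% |
| 1% | 0.190 | 4% | 31% |
| 2% | 0.036 | 0.1% | 7% |
| 3% | 0.007 | <0.1% | 1% |

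**Step 2. No events in either arm.** All residuals are zero, so the independence GEE gives 0 to 0. With an exchangeable working correlation and 10 sites, the fit failed in 150 of 150 runs. For the Miettinen-Nurminen score limit, the constrained estimates at difference d are d and 0, so d/(1-d) = 3.84 × 330/(329 × 165) = 0.0234 and d = 2.28 points.

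**Step 3. One empty arm, model without sex.** Take m events at m different sites out of K equal sites, and none in the other arm.
- Robust variance: m(1-m/K)/165².
- Model-based variance: p(1-p)/165, with p = m/165.

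Example, 2 v 0 with K = 10: the estimate is 2/165 = 1.21 and the robust SE is √(2 × 0.8)/165 = 0.77. The upper limit is 1.21 + 1.96 × 0.77 = 2.71. Using t(9) and a K/(K-1) variance correction, it is 3.04. The model-based limit is 2.88.

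| Events, PAC v control | GEE upper limit (10-29 sites; robust or model-based; z or t) | Miettinen-Nurminen |
|---|---|---|
| 1 v 0 | 1.7-2.0 | 3.4 |
| 2 v 0 | 2.7-3.0 | 4.3 |
| 3 v 0 | 3.5-3.9 | 5.2 |
| 0 v 1 | 0.5-0.8 | 1.7 |

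Events that share a site raise the robust limit. With 10 sites and z, two events at one site give 3.47, and three at one site give 5.20, which is no longer low. Two events fall at different sites with probability 0.90, and three do so with probability 0.72.

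**Step 4. One empty arm, sex in the model.** This is the covariate set stated for the primary GEE. In statsmodels with an independence working correlation, fits failed or were degenerate in about 75-80% of runs at 1 v 0, 35-40% at 2 v 0, and 90% or more at 0 v 1. A separate set of 150 runs gave 128/150 = 85% at 1 v 0 and 69/150 = 46% at 2 v 0, so the shares are approximate and depend on the set-up. Where the fit succeeded, the median upper limits agreed with Step 3 (about 1.7 at 1 v 0 and 2.7-2.8 at 2 v 0).

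**Step 5. Miss rate of the upper limit.** Exact enumeration, model-based interval, among trials with at least one event; nominal 2.5%.

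| Assumed risks, PAC v control | Upper limit below the true difference |
|---|---|
| 1.5% v 0.5% | 5.0% |
| 2% v 1% | 4.1% |
| 3% v 2% | 3.3% |
| 0.5% v 0.5% | 0.5% |
| 1% v 1% | 1.7% |
| 2% v 2% | 2.3% |

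At 1.5% v 0.5%, about 96% of the misses come from trials with one empty arm. With a robust SE and no between-site variation, simulation gives 6.7%, 5.8% and 5.6% for 10, 20 and 29 sites. The score interval misses in 0.4-1.2% of trials under these two excess-risk settings (1.5% v 0.5% and 2% v 1%), so it is conservative.

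**The case against.** Five points can be made against the concern.

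- **The short limits come from a model without sex.** A reader might infer that they follow whatever the protocol leaves open. They do not: with sex included, the usual result at one event is a visible failure, not a quietly short interval. This stands. It changes the form of the problem but does not remove it, because a rule that cannot be carried out for the expected data is also badly fixed.
- **Fallbacks belong in the SAP, which is not shown.** This stands for the missing fallback alone. The protocol does, however, name a method for every remaining binary outcome, and an SAP that follows it inherits the difficulty.
- **Coverage is not poor in general.** A reader might infer that the interval routinely understates harm. At equal risks of 0.5-1% it does not. At 1.5% v 0.5%, two-sided coverage among trials with any event is still 94.3%. The excess misses need very low risks together with a true excess on PAC. This stands.
- **The score method exaggerates the gap.** This stands in part. Some of the roughly 1.3-1.6 points at 2 v 0 is the score interval's own conservatism, so the nominal 2.5% is the fair yardstick.
- **The risks are assumed.** This stands. All-cause mortality in hospitalised adults could be 2% or more, and then empty arms are uncommon.

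**Conclusion.** The concern holds in a limited form, and its severity is minor. If both arms are empty, the prescribed analysis gives a zero-width interval or none. If one arm is empty, the sex-adjusted fit often fails. Where a fit is obtained and the events lie at different sites, the upper limit for excess harm is too low: 2.7-3.0 points at 2 v 0, against 4.3 by the conservative score method. Under an assumed 1.5% v 0.5%, the model-based upper limit misses about twice as often as it should (5.0% against 2.5%).

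This rests on assumed event risks, 165 per arm, site read as the GEE cluster, and failure rates from one software package.

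A reader might infer from the margin rationale that the non-inferiority conclusion is weakened. The document does not support that: the secondary objectives are exploratory, and no margin or test uses these intervals. The interim safety review rests on event numbers and the monitoring committee's judgement. The effect is confined to how two safety outcomes are reported.

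**What to change.** In section 20a, take 28-day mortality and drug-related SAEs out of the GEE rule. For these two, report event counts by arm and an unadjusted risk difference with a Miettinen-Nurminen 95% interval (Newcombe or exact would also serve). Keep GEE for the more frequent binary secondary outcomes. The interim needs no change.

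The cost is one sentence and standard software. The two outcomes lose adjustment for site and sex, which a handful of events can hardly support. The intervals become wider and somewhat conservative: at 2 v 0 the score interval runs from -1.1 to 4.3, a width of 5.4 points, against 3.0-3.7 with GEE.

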### Outcomes [12]

#### Primary outcome

Clinical cure 10 days (+/− 2 days, i.e. weekends) after antibiotic treatment completion defined as being alive with absence of fever (≥ 38.3 °C) and resolution of, or return to non-infected baseline of, urinary tract symptoms (as defined in inclusion criteria) without hospital readmission (for UTI symptoms) or additional antibiotic treatment (for UTI symptoms) based on a structured telephone interview performed by a centralised allocation-blinded study nurse.

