**Table 3 Tab3:**
[figure not shown]
Participant timeline

*PAC pivmecillinam and amoxicillin/clavulanic acid, TMX trimethoprim-sulfamethoxazole*

^*****^This refers to a sensitivity analysis for the primary outcome using retrospective medical journal review by the treating physician

^†^If information from the telephone interview assessor and the medical chart review assessor are divergent, we will always choose the conservative conclusion and stipulate failure (i.e. 1/0 1)

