## Assignment of interventions: blinding

### Who will be blinded {17a}

Trial participants and in-patient care providers will not be blinded to interventions in this pragmatic trial. Neither will the treating physician who assesses secondary endpoints 2-8. However, the central outcome assessor of the primary outcome will be blinded to interventions, as will the trial investigators, data analysts and author group. When data is extracted from the REDCap database, the allocation will be coded as “1” and “2” and the Code Key will only be revealed after statistical evaluation of the primary and secondary endpoints.

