## Data collection and management

### Plans for assessment and collection of outcomes {18a}

Baseline data and allocation will be entered into the REDCap database using a short and study-specific electronic case report form (eCRF) directly when assessing eligibility and assigning allocation by the physician who recruited the participant. The trial investigators will instruct a limited number of physicians at participating centre how to access and fill out the eCRF and provide a step-by-step guide and contact information for technical assistance. The primary outcome and the secondary outcomes 2-4 will be assessed using a semi-structured interview with a trial-specific guideline and entered into a separate part of the REDCap eCRF. The first 10 participants’ interview responses will be checked for conformity between at least two study nurses. The remaining secondary outcomes will be assessed retrospectively through medical chart review and from microbiological results by the recruiting physician at 30–60 days after the patient was allocated and then entered into a final separate part of the eCRF. The retrospective chart review will also serve as a sensitivity analysis to the telephone interview for the primary outcome and the secondary outcomes of early drug discontinuation and further antibiotic prescription. A copy of the REDCap eCRF (English) and semi-structured interview guideline (Swedish) can be sent on request.

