### Data management {19}

All data entry will be done electronically, except for code keys and informed consent forms. The eCRF in the REDCap database uses data range checks. The primary outcome and secondary outcomes 2-4 will be double-checked retrospectively against the medical journal by the treating physician 30–60 days after randomisation. Individual patient data will be handled as ordinary chart records and will be kept according to the European General Data Protection Regulation (GDPR). All original records (i.e. code keys and consent forms) will be retained in a locked cabinet at each participating centres infectious disease department for 25 years to allow inspection by relevant authorities. The coded trial database will be maintained for 25 years if requested for revision. Standardised data management procedures can be provided on request from Clinical Trials Sweden—Forum South.

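### The blinded primary outcome can be changed from cure to failure by a later unblinded chart review, and this one-way rule is not reliably conservative for non-inferiority

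*Protocol article*

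**What the plan says.** All references are to the protocol article.

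- **Source of the primary outcome.** Under Primary outcome, clinical cure 10 ± 2 days after treatment is "based on a structured telephone interview performed by a centralised allocation-blinded study nurse". Who will be blinded {17a} confirms that "the central outcome assessor of the primary outcome will be blinded to interventions".
- **Chart review.** Data management {19} states: "The primary outcome and secondary outcomes 2-4 will be double-checked retrospectively against the medical journal by the treating physician 30–60 days after randomisation". Plans for assessment and collection of outcomes {18a} has the review done "by the recruiting physician at 30–60 days after the patient was allocated".
- **Blinding of the reviewer.** After saying that participants and in-patient care providers are not blinded, {17a} adds: "Neither will the treating physician who assesses secondary endpoints 2-8". Under Implementation {16c}, the physicians who enrol patients also assign the intervention.
- **Rule for disagreement.** For differences between interview and chart on the primary outcome, Statistical methods {20a} says "we will always choose the conservative option and consider this a failure". A footnote to Table 3 repeats it: "we will always choose the conservative conclusion and stipulate failure".
- **Second description of the same review.** Section {18a} says: "The retrospective chart review will also serve as a sensitivity analysis to the telephone interview for the primary outcome". The other Table 3 footnote and the third sensitivity analysis in Methods for additional analyses {20b} describe it in the same way.

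**The concern.** The trial is open-label for patients and treating staff, and most of the primary outcome is subjective. The blinded interview is therefore an important safeguard. The disagreement rule lets a second source, held by someone who knows the allocation, change the blinded result in one direction. Three things are left loose.

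1. **Scope.** The rule covers any component of the primary outcome. That includes symptoms, and the judgement whether a prescription or readmission was for UTI.
2. **Time.** The endpoint is tied to 10 ± 2 days after treatment. The text says when the chart is reviewed, but not up to what date a chart event counts.
3. **Role.** The same review is part of the primary outcome in one place and a check on it in others.

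The rule is called conservative. Scoring doubtful cases as failures does not protect a non-inferiority claim in the way it may protect a superiority claim. Extra failures in control move the risk difference in favour of the new treatment, and extra failures in both arms shrink a true deficit. At stake are the type I error of the non-inferiority claim and the power of the trial.

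**Working it through.** **Inputs from Sample size {14} and Trial design {8}.** Cure 93% (taken for both arms), margin 10 points, one-sided alpha 2.5%, 300 evaluable patients at 1:1 (150 per arm), stated power 90%.

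**Input not in the documents.** The share *f* of cures that the chart review wrongly recodes as failures. I assume 3% and 5%. In control, 3% is 0.03 × 0.93 × 150 ≈ 4 patients.

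**The plan's own figure first.** A simulation of 30 sites with 10 patients each, intraclass correlation 0.1 and identity-link GEE with robust standard errors gives 89.9% power under simple randomisation with independence working correlation. With exchangeable correlation it gives 92.4%, and with randomisation balanced within site 93.5%. The stated 90% is reproduced, so the sample size is not in question. The closed form below, without clustering, gives 92.4% and serves as the baseline.

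**Formula.** With p_C and p_T the recorded cure rates in control and intervention,

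SE = √[p_C(1 − p_C)/150 + p_T(1 − p_T)/150]

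P(claim non-inferiority) = Φ[(0.10 + p_T − p_C)/SE − 1.96]

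This is power when the true rates are 93% and 93%, and type I error when they are 93% and 83%. A false-override share *f* in an arm multiplies its cure rate by (1 − *f*).

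**No overrides.** True equality: SE = 0.0295, Φ(0.10/0.0295 − 1.96) = Φ(1.43) = 92.4%. True −10 points: Φ(−1.96) = 2.5%.

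**Equal, 3%.** Power: both rates 0.9021, SE = 0.0343, Φ(0.95) = 83.0%. Type I error: rates 0.9021 and 0.8051, difference −9.7 points, SE = 0.0404, Φ(−1.89) = 3.0%.

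**Equal, 5%.** Power: both rates 0.8835, SE = 0.0370, Φ(0.74) = 77.0%. Type I error: difference −9.5 points, SE = 0.0424, Φ(−1.84) = 3.3%.

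**Control only, 3%, true −10 points.** Rates 0.9021 and 0.83, difference −7.2 points, SE = 0.0391, Φ(−1.25) = 10.6%.

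**Intervention only, 3%.** Power: rates 0.93 and 0.9021, difference −2.8 points, SE = 0.0320, Φ(0.29) = 61.6%. Type I error falls to 0.5%.

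| False overrides | Power | Type I error |
|---|---|---|
| none | 92.4% | 2.5% |
| 3% in both arms | 83.0% | 3.0% |
| 5% in both arms | 77.0% | 3.3% |
| 3% in control only | 97.9% | 10.6% |
| 3% in intervention only | 61.6% | 0.5% |

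**The opposite error.** If instead the interview misses a share *g* of true failures in both arms and nothing corrects it, a true 93% against 83% is recorded as 1 − 0.07(1 − *g*) against 1 − 0.17(1 − *g*). For an assumed *g* of 10% the difference shrinks to −9 points and type I error is 4.7%. For 20% it is −8 points and 8.6%.

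**The case against.** The best defence is that the chart check corrects a real weakness. The only example given in {20a} is a prescription that the patient does not mention but the chart shows, which is a true failure that the interview missed. Unrecovered missed failures also favour non-inferiority: the 4.7% and 8.6% above exceed the 3.0–3.3% from equal false overrides. This stands, and it is why chart events should be kept. It does not justify letting an unblinded reviewer overrule the interview on symptoms or on attribution to UTI.

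It can also be said that {20b} already plans to report chart-based against interview-based results, so an effect of the override would be visible. That is partly true, but the comparison does not govern the non-inferiority claim. The concordance requirement in {20c} covers only the ITT, mITT and PP populations. The word also in {18a} suggests deliberate dual use rather than a slip, but the text still has to say which version is primary.

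A reader might infer more than the text supports:

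- **That the physician decides every disputed case.** An interview failure is never reversed by a chart cure. The reviewer matters only where the interview says cure and the chart says failure.
- **That a prescription on day 50 undoes a cure.** The 30–60 days are when the review is done, not a stated event window. The endpoint definition keeps its own date, and follow-up is 28 days. The gap is that no chart cut-off is written; the eCRF or the full protocol may supply one.
- **That the endpoint is simply unblinded and anti-conservative.** The interview stays blinded, and overrides that fall mainly on the intervention arm work against the claim.
- **That the protocol calls blinded assessment its main protection.** The Methodology part of the Discussion names it beside the three analysis populations.

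**Conclusion.** The point holds in a limited form. A stated rule brings unblinded judgement into a primary outcome that is defined as blinded. It works in one direction only, has no written event cut-off, and conflicts with the description of the same review as a sensitivity analysis. The rule is not reliably conservative. Equal false overrides chiefly cost power and barely move type I error. An excess in control raises type I error materially, and an excess in the intervention arm lowers both power and type I error.

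The sizes rest on assumed rates of 3% and 5%, on every override being false, and on a calculation without clustering. The documents give neither an override rate nor a difference between arms, so the control-only and intervention-only rows are bounds for illustration, not forecasts. The rule should be corrected before the code is broken. It does not by itself invalidate the trial.

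**What to change.** Reconcile Primary outcome, the Table 3 footnotes, {18a}, {20a} and {20b} into one rule:

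1. Fever and symptom items come only from the blinded interview.
2. The chart may add only dated objective events (death, readmission, antibiotic prescription) up to the test-of-cure date.
3. In discordant cases, the central blinded assessor decides whether the event was for UTI, from an extract that does not show the allocation.
4. The version in which any disagreement counts as failure, and the chart-only version, are reported as sensitivity analyses.
5. The word conservative is dropped from the description of the rule.

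The cost is a change of wording, one event-date field in the chart-review part of the eCRF, and masked extracts for the discordant cases, which should be few. An antibiotic's name may reveal the allocation, so the extract should carry the date and indication of a prescription without details of the study drug.
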